# A Virtual Self-Management Intervention for Adolescents With Juvenile Idiopathic Arthritis: Protocol for the VISTA-JIA Randomized Controlled Trial

**DOI:** 10.2196/69539

**Published:** 2025-06-27

**Keywords:** juvenile idiopathic arthritis, self-management program, randomized controlled trial, videoconference, virtual intervention, peer support

## Abstract

**Background:**

Needs assessments in patients with juvenile idiopathic arthritis (JIA) have revealed a need for disease information, self-management skills, and peer support. We previously developed and tested the acceptability of an in-person and videoconference-based self-management program (SMP) to address these needs.

**Objective:**

The aim of this pilot randomized controlled trial (RCT; the VISTA-JIA trial) is to evaluate the feasibility and preliminary effectiveness of a virtual group-based SMP for adolescents with JIA in comparison to a waitlist control group.

**Methods:**

A total of 100 participants with confirmed JIA (aged 12-17 years) will be recruited from 5 Canadian pediatric rheumatology centers and randomized 1:1 to the intervention or waitlist control groups. Adolescents in the intervention group will receive the virtual SMP. Those randomized to the control group will receive standard of care alone and will later be eligible for the SMP. The SMP includes JIA disease education, self-management strategies, and peer support. Four 60- to 90-minute sessions will be conducted over 8 weeks with a group size of 4-6 participants. The primary feasibility outcome will be adherence to the SMP (defined as completion of all 4 sessions by at least 80% of participants). Other secondary feasibility outcomes will include recruitment and withdrawal rates, the proportion of completed questionnaires, engagement and satisfaction with the SMP measured through a semistructured virtual interview, and intervention fidelity (consistent content and technology delivery). Secondary preliminary effectiveness outcomes will be assessed by completing 5 validated questionnaires at pre- and postprogram time points: (1) the Medical Issues, Exercise, Pain, and Social Support Questionnaire to assess perceived ability to manage JIA (self-management); (2) the Children’s Arthritis Self-Efficacy Scale to assess self-efficacy; (3) the Pediatric Quality of Life Inventory 3.0 Rheumatology–Teen Module to assess health-related quality of life; (4) the PROMIS (Patient-Reported Outcomes Measurement Information System) Pediatric Pain Interference Scale to assess pain interference; and (5) Readiness for Adult Care in Rheumatology to assess transition readiness. Descriptive statistics and nonparametric tests will be used to analyze the data.

**Results:**

The study setup is complete at all centers, including training of the facilitators, revising and finalizing education sessions, participant’s handout guide, and fidelity checklist. Recruitment began in January 2024 and is expected to conclude by December 2025. Feasibility outcomes, including adherence and engagement, as well as preliminary effectiveness, will be analyzed post intervention.

**Conclusions:**

This is the first evidence-based, virtual, interactive, group-structured JIA SMP in Canada. This SMP will address needs for disease information, self-management skills, and peer support in adolescents with JIA. The results of this pilot study will inform a full-scale RCT focused on the efficacy and cost-effectiveness of the program with the goal of integration in routine clinical practice across Canada.

**Trial Registration:**

ClinicalTrials.gov NCT06184100; https://clinicaltrials.gov/study/NCT06184100

**International Registered Report Identifier (IRRID):**

DERR1-10.2196/69539

## Introduction

### Background

Juvenile idiopathic arthritis (JIA) is the most common childhood rheumatic disease with an estimated prevalence of 1 in 1000 children younger than 16 years [1]. Although treatments for JIA have improved over the last decade, many affected children experience continued disease activity and related morbidity, long-term disability, and an increased incidence of psychosocial complications as they enter adulthood [2]. Adolescence is a critical period of physical, cognitive, and psychosocial development as the youth develop skills, emotional regulation, and independence to manage changes in responsibilities and prepare to assume adult roles [3]. In adolescents with JIA, this period translates to a requirement for additional self-management skills (eg, medical decision-making and patient-provider communication) as their autonomy increases and as they assume greater responsibility for the management of their disease to prepare for transition into adulthood and adult health care. Unfortunately, 25%-75% of adolescents with JIA are lost to follow-up once transferred from pediatric to adult health care in Canada [4-8]. Needs assessments have revealed insufficient time to provide transition services, a lack of reliable JIA information accessible to adolescents and knowledge about linkages to community resources, need for additional self-management skills, and a gap in peer support in adolescents with JIA [9-13]. These gaps were found to be critically important to address within individual countries through distinctively customized plans and activities [4,14].

### Peer Support and Self-Management Programs

Self-management programs (SMPs) are proposed as effective ways to address the educational, self-management, and peer support needs for adolescents with JIA. Significant evidence from adult and pediatric medicine has indicated that SMPs result in improved health behavior, self-efficacy, and certain health status outcomes in persons with arthritis [15,16]. SMPs afford the opportunity to instantly react to participant feedback, tailor the amount and complexity of information to participants’ needs [17,18], and immediately address information that participants do not understand. Furthermore, SMPs in a small group setting allow for interaction and discussions among participants, which, in turn, builds social support [15]. Remotely delivered SMPs, in the form of videoconferencing, represent an evolving technology that can improve accessibility, especially for patients residing in rural or remote communities [19].

Previous needs assessments [12-14] have identified the need for virtual self-management interventions incorporating peer support and for standards of technology delivery and guidance for effective virtual communications in a group setting [20,21].

Our aim is to conduct a pilot multicenter randomized controlled trial (RCT) to evaluate the feasibility and preliminary effectiveness of a virtual group-based SMP for adolescents with JIA in comparison to a waitlist control group.

## Methods

### Study Design

A pilot RCT will be conducted to determine the feasibility and preliminary effectiveness of a virtual SMP intervention. Eligible participants will be randomized 1:1 to either the intervention group or a waitlist control group. Both groups will complete baseline measures (T0) as well as postprogram measures (T1). Participants enrolled into the intervention will undergo the SMP and be asked to participate in an optional postintervention interview. The waitlist control group will continue receiving standard of care during this program period. They will be given the option to complete the SMP afterwards, and if completed, be asked to complete postintervention questionnaires. They will also be asked to participate in the optional postintervention interview. The study is registered in ClinicalTrials.gov (NCT06184100). Figure 1 shows the trial schema, and Multimedia Appendix 1 shows the timeline. This study follows the SPIRIT (Standard Protocol Items: Recommendations for Interventional Trials; checklist provided in Multimedia Appendix 2) guidelines.

**Figure 1 figure1:**
[figure not shown]
Trial schema.

### Participants

Participants will be recruited from 5 Canadian pediatric rheumatology centers across different provinces after obtaining local research ethics approval. Sociodemographic and disease-related characteristics including age, gender, disease subtype, date of diagnosis, and current or past treatment will be collected from health records for descriptive purposes at baseline.

### Inclusion Criteria

Participants will be considered eligible to participate if they meet the criteria described below:

Adolescents between the ages of 12 and 17 years.Confirmed diagnosis within 5 years according to the International League of Associations for Rheumatology JIA classification criteria.Followed up in one of the pediatric rheumatology clinics participating in the RCT.Able to access the internet.Willing and able to complete web-based measures.

### Exclusion Criteria

Individuals will be excluded from the RCT if they meet any of the following criteria:

Insufficient English reading and speaking skills.Untreated psychiatric or comorbid disorders or major cognitive impairments leading to an inability to understand materials and participate in the SMP group activities.Other chronic conditions such as other autoimmune disease, neurologic, orthopedic, and organ system disorder (eg, heart and kidney) that might influence outcome assessments.Past participation in the last year or participating in another formal peer-support or self-management program.Additionally, concomitant adjunct interventions and other involvement with peer support groups (contamination) will be recorded.

### Randomization, Recruitment, and Sample Size

CONSORT (Consolidated Standards of Reporting Trials; checklist provided in Multimedia Appendix 3) 2010 guidelines suggest a sample size calculation of 9% of the anticipated full-scale RCT for the intervention group in pilot studies [22,23]. However, to establish feasibility at several sites and get an estimate of a statistically significant SD to inform a full-scale multicenter trial, our target is to conduct 2 offerings of the program with 4-6 participants per group at each of the 5 sites to control for site-specific education. Eligible participants will be identified through a review of the patient database and will be contacted by research coordinators. Some participants will also be recruited during their clinic visits. They will receive detailed information about the study, including its objectives, procedures, and potential benefits. Interested participants will provide informed consent (or assent, with parental consent for minors). The study aims to recruit a total of 100 participants. Therefore, we will require 50 participants in the intervention group and 50 in the waitlist control group. This sample size was chosen to establish feasibility and inform a larger multicenter trial. Participants will be randomized 1:1 to either the intervention group or the waitlist control group using block randomization with variable block sizes. This randomization will be conducted using REDCap (Research Electronic Data Capture; Vanderbilt University), a secure web-based application for managing data. Randomization will occur before baseline measures are completed. Participants in the intervention groups will be from the same center to adapt the program to local health care systems and account for the variability of nonformal educational practices between centers. This approach will also facilitate an evaluation/subgroup analysis of outcome measures at each center.

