### Outcome Measures

#### Feasibility Outcomes

Primarily, feasibility will be measured through adherence with the SMP (defined as 80% completion). Other feasibility outcomes will include the following:

Recruitment and withdrawal rates (>80% recruitment rate and <80% withdrawal).The proportion of completed questionnaires (defined as 80% when all measures are completed) at baseline and 8 weeks post randomization in both groups.Satisfaction with the SMP as measured through questionnaires and a semistructured virtual interview with the participants following involvement in the SMP to capture the participants’ experience.Intervention fidelity (defined as consistent content and technology delivery) will be assessed by fidelity checklists and qualitative analysis of recorded video sessions after 2 sessions, 4 sessions, and at completion of all sessions to ensure that sessions are consistently delivered and as planned.

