#### Preliminary Effectiveness Measures

Participants of both the intervention and control groups will complete 5 validated and reliable patient-reported outcome measures on the web at baseline and post program. This includes the following:

The Medical Issues, Exercise, Pain, and Social Support Questionnaire—a validated (eg, concurrent validity and construct validity) and reliable (eg, internal consistency) measure for perceived ability (eg, knowledge, skill, behavior, attitudes, and self-efficacy) to manage JIA [25].The Children’s Arthritis Self-Efficacy Scale—a validated (eg, concurrent validity and construct validity) and reliable (eg, internal consistency) measure for arthritis self-efficacy [26].The Pediatric Quality of Life Inventory 3.0 Rheumatology–Teen Module—a validated (eg, construct validity and concurrent validity) and reliable (eg, internal consistency) measure used for pediatric rheumatology–specific health-related quality of life in children aged 13-18 years [27].The PROMIS (Patient-Reported Outcomes Measurement Information System) Pediatric Pain Interference Scale—a validated (eg, concurrent validity and construct validity) and reliable (eg, internal consistency) measure for pain behavior in children aged 8-17 years [28].Readiness for Adult Care in Rheumatology—a validated (eg, concurrent validity and construct validity) and reliable (eg, internal consistency) measure to assess transition readiness in adolescents with JIA [29].

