##### Preliminary Effectiveness Outcomes

The quantitative data will be entered into SPSS [34]. Descriptive statistics will be used to analyze the patient-reported outcome measures with an ordinal Likert scale at baseline and immediately post intervention. In addition, nonparametric Wilcoxon signed rank tests will be used to assess if there is a significant difference between a pre- and posttest outcome. Nonparametric tests will be used due to the small sample size and a lack of normally distributed data. Changes in pre- and posttest outcomes will be analyzed over time using a repeated measures mixed linear model approach where participants will be included as the random effect and baseline scores, study site, and disease-related characteristics will be used as fixed factors or covariates.

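### Randomisation precedes the self-reported baseline in an unblinded waitlist trial, so T0 scores and T0 completion can depend on arm and bias the secondary effectiveness analyses

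*Protocol article*

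**What the plan says.** The order of procedures is explicit. Under Randomization, Recruitment, and Sample Size the article says: "Randomization will occur before baseline measures are completed". No other section changes this, and none describes keeping the allocation from participants until T0 has been answered.

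The comparison is open by nature. The intervention arm attends live videoconference sessions, while Study Design says of the other arm: "The waitlist control group will continue receiving standard of care during this program period".

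Under Preliminary Effectiveness Measures, both arms "will complete 5 validated and reliable patient-reported outcome measures on the web at baseline and post program".

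Preliminary Effectiveness Outcomes uses T0 in two ways:
- as the pre value: "nonparametric Wilcoxon signed rank tests will be used to assess if there is a significant difference between a pre- and posttest outcome";
- as a covariate in the mixed model, where "baseline scores, study site, and disease-related characteristics will be used as fixed factors or covariates".

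T0 completion is also an outcome. Feasibility Outcomes sets an 80% criterion for questionnaire completion at baseline and follow-up in both groups. The primary outcome in that section is adherence to the programme, which needs no T0 score.

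**The concern.** A baseline measured before allocation is the same in expectation in both arms. One measured after allocation has that protection only if the participant does not yet know the arm. An adolescent who has just been offered the programme, or told to wait, may answer questions on self-efficacy, pain interference or quality of life differently, and one told to wait may not answer at all.

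Two things follow if the arm is known at T0:
- Subtracting T0 or adjusting for it carries any arm-related shift in T0 into the estimated effect.
- Losses between randomisation and T0 may differ by arm, so the analysed groups may no longer be the randomised groups, and the baseline-completion rate would partly reflect reaction to allocation.

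The preliminary effects, the SDs and the completion rates are all meant to inform the full-scale trial, so an error here could be carried forward.

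**Working it through.** **Sample size used.** 5 sites × 2 offerings × 4 to 6 participants gives 40 to 60 in the intervention arm. At 5 per group this is 50, and 1:1 allocation gives 100, which matches the article.

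**Assumed inputs.** The article gives none of these:
- *s*: shift in T0, intervention minus waitlist, caused by knowing the arm; 0.2 SD, range 0.1 to 0.3.
- *r*: correlation of T0 with T1; 0.6, range 0.5 to 0.7.
- *p*: fraction of the shift still present at T1; 0 or 1.

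**Formulas, with no true programme effect.** The arms differ by *s* at T0 and by *ps* at T1.
- Baseline-adjusted (ANCOVA) bias = (*p* − *r*)*s*. ANCOVA stands in for the baseline-adjusted model.
- Change-score bias = (*p* − 1)*s*. The article names no between-arm change-score test, but an arm-by-time contrast from a model with T0 as one of the repeated measures would behave this way.
- SE, ANCOVA = √(2(1 − *r*²)/50) = √(2 × 0.64/50) = 0.16 SD.
- SE, change score = √(4(1 − *r*)/50) = √(1.6/50) = 0.179 SD.

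**Results at *s* = 0.2, *r* = 0.6**

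| Shift at T1 | ANCOVA bias | Change-score bias |
|---|---|---|
| gone (*p* = 0) | −0.12 SD; 0.12/0.16 = 0.75 SE | −0.20 SD; 0.20/0.179 = 1.12 SE |
| fully present (*p* = 1) | +0.08 SD; 0.08/0.16 = 0.50 SE | 0 |

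The signs reverse if *s* is negative.

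**Range, with the shift gone by T1.** At *r* = 0.6, shifts of 0.1 to 0.3 SD give an ANCOVA bias of 0.06 to 0.18 SD in size. At *s* = 0.2, *r* of 0.5 to 0.7 gives 0.10 to 0.14 SD.

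**Error rates, by simulation.** No true effect, 50 per arm, intervention T0 lowered by the stated amount, shift gone by T1. ANCOVA rests on 20,000 trials per setting and the signed rank test, run within the shifted arm, on 2,000.

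| Shift | ANCOVA type I error, *r* = 0.5 / 0.7 | Signed rank false positives, *r* = 0.5 / 0.7 |
|---|---|---|
| 0 | 4.8% / 5.1% | about 5% / about 5% |
| 0.1 SD | 6.0% / 7.7% | not run |
| 0.2 SD | 8.6% / 16.5% | 28% / 39% |
| 0.3 SD | 13.3% / 29.4% | 54% / 76% |

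**Completion.** The 80% criterion does not say whether each arm must meet it. If 95% of the intervention arm and 70% of the waitlist arm completed T0 (assumed rates), the pooled figure would be (95 + 70)/2 = 82.5%. That passes while the waitlist arm falls short, with an expected 47.5 against 35 baselines.

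**The case against.** The strongest reply is that the article says when randomisation happens, not when the participant is told the result. If allocation is withheld until T0 is complete, the problem largely disappears, and a condensed article may leave that step to the full protocol. This stands as a limit: a reader might infer that adolescents do answer T0 knowing their arm, but the article does not say so. The explicit ordering remains, and no safeguard is attached to it.

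Second, this is a pilot. A reader might infer that all its results are compromised. They are not. Adherence uses no T0 score, nor do recruitment, withdrawal, satisfaction or fidelity. An unadjusted comparison of T1 scores does not use T0 either. The Significance section leaves proof of effectiveness to a larger trial.

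Third, the size of the bias depends on how long the reaction lasts. With full persistence the change-score bias vanishes and the adjusted bias changes sign, so neither a fixed direction nor a fixed size can be claimed. It would also be wrong to divide the 0.20 SD change-score bias by the ANCOVA standard error, which gives 1.25; its own standard error gives 1.12.

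Fourth, the 80% criterion might be read as accepting 20 of 100 participants without T0. It is a feasibility threshold, not a tolerance for missing data in the effectiveness analysis. Missing Data Considerations already plans to examine missing-data patterns at the study time points, though it does not say by arm.

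**Conclusion.** The point holds in limited form and should be fixed, but it does not invalidate the pilot. Unless allocation is withheld until T0 is complete, the stated order lets T0 scores and T0 completion depend on arm. The analyses exposed are the pre-post signed rank tests, the baseline-adjusted mixed model and the baseline-completion rate.

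Under the base assumptions the bias in the adjusted estimate lies between 0.12 SD one way and 0.08 SD the other, according to persistence. That is not negligible beside a standard error of 0.16 SD. The actual direction and size cannot be known from the article.

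Moving T0 closes the route through the baseline. It does not remove any reaction to allocation that is still present in the T1 answers; that comes from the lack of blinding and is there under either order.

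**What to change.** **Change the order.** Replace the sentence on timing in Randomization, Recruitment, and Sample Size with a rule that all T0 questionnaires must be complete in REDCap before a participant can be randomised. At minimum, state that allocation is not disclosed to the participant until T0 is complete. If that is already the practice, say so.

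**Adjust the completion outcome.** If randomisation is gated on T0, baseline completion becomes 100% by construction among those randomised. Define it among consented adolescents instead, and report follow-up completion by arm.

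**Handle those already in the trial.** The Results overview reports 40 enrolled by March 2025, so up to about 40 of the planned 100 may fall under the present order at that date, plus any randomised since. For them, report T0 completion and T0 timing by arm. Add a sensitivity comparison of T1 scores between arms that leaves out the self-reported baseline, which keeps everyone with T1 data. Excluding these participants should be only a further check, because dropping 40 would leave at most 60.

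**Cost.** A REDCap gating rule and a short amendment at the participating sites, for which the article lists five ethics approvals. A few consented adolescents who never complete T0 will not be randomised. The unadjusted T1 comparison is less precise (SE √(2/50) = 0.20 SD, against 0.16 SD with adjustment at *r* = 0.6). The target of 100 does not change.

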### Intervention

The program consists of JIA disease education, self-management strategies, and peer support in a group-based setting. Four sessions, 60-90 minutes each, will be conducted over 8 weeks with a group size of 4-6 participants via videoconferencing platforms. Each session will include Microsoft PowerPoint–delivered presentations, interactive activities, and group discussions. The 4 sessions will focus on the following themes: Overview and Diagnosis of JIA, Daily Living and Exercise, Coping Strategies, and Medication and Lifestyle Management. To ensure intervention fidelity, sessions will be provided by the same designated health care professionals. All sessions will be video-recorded and uploaded to a secured research server to assess the group’s dynamic and ensure sessions are delivered as planned (fidelity). Young adults living with JIA from participating centers will be asked to sit in during these sessions to share their lived experiences and foster peer social support. Additionally, each site will include site-specific resources. After completing the intervention, participants will be asked to independently attend an optional semistructured interview to capture participant experiences of the intervention.

